**Figure 1 F1:**
[figure not shown]
Study flow diagram. DTI, diffusion tensor imaging; OS, overall survival; PFS, progression-free survival.

### Study procedures: clinical evaluations and follow-up

Preoperative (baseline) CRF (Case Report Form).Unique subject ID, demographics (centre, year, gender, age), tumour-specific factors (tumour volume preoperative, tumour hemisphere and lobe; eloquent areas), patient specific factors: preoperative KPS, ASA score, neurological status (NIHSS), MRC grade arm/leg (for motor-eloquent tumors), neurolinguistic testing, MOCA, QoL questionnaires (QLQ-C30, QLQ-BN20, EQ-5D).Surgery CRFType of ISM, surgeon’s rationale for modality, surgeon’s goal, use of preoperative steroids (if yes: clinical improvement, conversion to mapping possible); use of surgical adjuncts (if DTI: integrity of tracts), use of additional imaging, radiological factors: resection percentage (both the contrast-enhancing and non-contrast-enhancing part), residual volume and postoperative ischaemia.Follow-up CRFsSix weeks postoperatively: histology and molecular markers (WHO grade, MGMT status, IDH-1 status), neurological status (NIHSS), MRC grade arm/leg, status MRC arm/MRC leg/facialis/speech/visual (new, worsened, improved, stable), KPS, QoL questionnaires (QLQ-C30, QLQ-BN20, EQ-5D).Three months postoperatively: neurological status (NIHSS), MRC grade arm/leg, status MRC arm/MRC leg/facialis/speech/visual (new, worsened, improved, stable), KPS, neurolinguistic testing, MOCA, QoL questionnaires (QLQ-C30, QLQ-BN20, EQ-5D).Six months postoperatively: neurological status (NIHSS), adjuvant treatment, MRC grade arm/leg, status MRC arm/MRC leg/facialis/speech/visual (new, worsened, improved, stable), KPS, MOCA, QoL questionnaires (QLQ-C30, QLQ-BN20, EQ-5D).Twelve months postoperatively: PFS, OS (end of study).

### Outcomes

#### Primary outcome measures

The primary outcomes are (1) proportion of patients with NIHSS deterioration at 6 weeks, 3 months and 6 months postoperatively; deterioration is defined as an increase of at least one point on the total NIHSS score compared with this score at baseline and (2) residual tumour volume of the contrast-enhancing and non-contrast enhancing part, as assessed by a neuroradiologist on postoperative T1 with contrast and T2/FLAIR MRI scan sequences using manual or semiautomatic volumetric analyses (Brainlab Elements iPlan CMF Segmentation, Brainlab AG, Munich, Germany or similar software).

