**Methods and analysis:**

This study is an international, multicenter, prospective three-arm cohort study of observational nature. Consecutive HGG patients will be operated with awake mapping, asleep mapping or no mapping with a 1:1:1 ratio. Primary endpoints are: (1) proportion of patients with National Institute of Health Stroke Scale deterioration at 6 weeks, 3 months and 6 months after surgery and (2) residual tumour volume of the contrast-enhancing and non-contrast-enhancing part as assessed by a neuroradiologist on postoperative contrast MRI scans. Secondary endpoints are: (1) overall survival and (2) progression-free survival at 12 months after surgery; (3) oncofunctional outcome and (4) frequency and severity of serious adverse events in each arm. Total duration of the study is 5 years. Patient inclusion is 4 years, follow-up is 1 year.

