### Sample size

This study has two primary endpoints. In order to guarantee that the overall type I error rate does not exceed 5%, we apply a weighted Bonferroni correction for multiple testing. The sample size calculations that follow take that into account. For the first primary endpoint, proportion of patients with neurological deterioration at 6 weeks postsurgery, we assume a deterioration rate of 10% in the control group (arm 3: no mapping), and 3% in the experimental groups (arm 1 and 2: awake and asleep mapping). A two-sample test for proportions with continuity correction requires 411 patients (137 per arm) in total in order to detect the above-mentioned difference of 7% with 80% power at a 4% significance level. For the second primary endpoint, proportion of patients without residual contrast-enhancing tumour on postoperative MRI, we assume a success rate of 25% in the control group (arm 3: no mapping), and 50% in the experimental groups (arm 1 and 2: awake and asleep mapping). A two-sample test for proportions with continuity correction requires 188 patients (94 per arm) in total in order to detect the above-mentioned difference of 25% with 80% power at a 1% significance level. In order to power the study for both primary endpoints, we should include the larger required number of patients, that is, 411. A total of 411 eligible and evaluable patients in three arms allow the difference of 25% in proportion of patients without residual tumour to be detected with 88% power. Taking into account possible ineligibility and withdrawal of consent (we estimate this at 10%), a total of 453 patients will be included (151 patients per arm).

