### Primary study parameters

The primary endpoints will be analysed using multivariate logistic regression. Subgroup analyses for tumour grade (WHO grade III/IV), preoperative neurological morbidity, preoperative tumour volume, patient’s age (in 10-year age brackets) and tumour location/eloquence will be performed.

We will be including a stratification factor in the primary analysis model with each 10 observed events using the order of prognostic value as mentioned in the paragraph above, where the first 10 events will be used to estimate the effect of the arm. This rule will be applied in case less than 40 patients in total develop neurological deterioration. In the so constructed multivariate logistic regression model the treatment arm effect will be tested at 4% significance level. The primary analysis of proportion of patients without residual contrast-enhancing and non-contrast-enhancing tumour consist of a multivariate logistic regression, where arm effect is corrected for all minimisation factors. In this model the group effect will be tested at 1% significance level. Manual or semiautomatic segmentation will be performed on axial T1 and T2/FLAIR MRI contrast enhanced slices to measure preoperative and postoperative tumour volume. A determination of volumes will be calculated blinded for the treatment group.

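### The first primary endpoint lists three NIHSS visits, but only 6 weeks is sized and the 4% test names no visit, so the 5% error guarantee is not secured for the endpoint as defined

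*Protocol article*

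**What the plan says.** All references are to the protocol article.

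- **Abstract, Methods and analysis:** the first primary endpoint concerns NIHSS "deterioration at 6 weeks, 3 months and 6 months after surgery".
- **Primary outcome measures:** it is the "proportion of patients with NIHSS deterioration at 6 weeks, 3 months and 6 months postoperatively", where deterioration means a rise of at least one point in total NIHSS over baseline.
- **Sample size:** "This study has two primary endpoints". The first is given as "proportion of patients with neurological deterioration at 6 weeks postsurgery", with rates of 10% without mapping and 3% with mapping, 80% power and 4% alpha. The second, absence of residual contrast-enhancing tumour, gets 1%. The reason for the split is explicit: "In order to guarantee that the overall type I error rate does not exceed 5%, we apply a weighted Bonferroni correction for multiple testing".
- **Primary study parameters:** in one logistic model, "the treatment arm effect will be tested at 4% significance level". No visit is given. A rule limits the number of covariates according to how many patients deteriorate, again without saying at which visit.

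**The concern.** The same endpoint has two definitions. The abstract and the outcomes section have three visits; the sample size section has one. The analysis section, which could settle the matter, is silent. The weighted Bonferroni split counts two primary endpoints, so it pays for one NIHSS decision and one residual-tumour decision. If the outcomes section governs, there are three NIHSS proportions and no rule for turning them into one decision.

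Two things are at stake. A favourable result at any of the three visits could be reported as the primary outcome while still pointing to the published definition. And the 5% guarantee, which the article states outright, would then rest on a choice of visit that has not been fixed.

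**Working it through.** **Inputs.** From Sample size: rates 10% and 3%, power 80%, alpha 4% (endpoint 1) and 1% (endpoint 2), continuity correction, 411 patients (137 per arm). From Study design: 1:1:1 allocation. The correlation between the visit-specific test statistics is in no document. It is an assumption and is varied below.

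**1. The plan's own figure.** With control size n, mapping arms pooled (ratio k = 2), difference d = 0.07 and a one-sided 4% test (z = 1.751; z for 80% power = 0.842):

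- Pooled rate: (0.10 + 2 × 0.03)/3 = 0.0533.
- n = [1.751 × √(1.5 × 0.0533 × 0.9467) + 0.842 × √(0.10 × 0.90 + 0.03 × 0.97/2)]² / 0.07² = 116.
- Continuity correction: (116/4) × [1 + √(1 + 2 × 3/(116 × 2 × 0.07))]² = 136.6, so 137.
- Total: 137 + 274 = 411, as stated.

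The 411 is thus the size for a single test of a single proportion, using the 6-week rates. Two-sided with the same correction, the totals would be 492 (2:1) or 235 per arm (1:1); the article does not state sidedness.

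**2. One NIHSS test, at 6 weeks.** Bonferroni sum: 4% + 1% = 5%. The guarantee holds.

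**3. Each visit tested at 4%, any one sufficient.** This is a hypothetical rule.

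- Independent visits: 1 − 0.96³ = 11.5%. Adding 1% for endpoint 2 gives 12.5%.
- Upper bound whatever the dependence: 3 × 4% + 1% = 13%.
- Correlated visits: simulation with three equicorrelated normal statistics, two-sided 4% each, 2,000,000 draws.

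| Assumed correlation | Any of three at 4% | Plus 1% |
|---|---|---|
| 0 | 11.5% | 12.5% |
| 0.5 | 10.2% | 11.2% |
| 0.7 | 8.9% | 9.9% |
| 0.8 | 8.0% | 9.0% |
| 0.9 | 6.8% | 7.8% |
| 1 | 4% | 5% |

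The total exceeds 5% at every correlation below 1. The same patients are compared with the same baseline score, so the lower rows are more plausible than independence.

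**4. Other rules that would fit three visits.** One composite (deterioration at any visit), one repeated-measures test, or a requirement that all three visits be significant would each be a single 4% decision and would not inflate the error. None of them is stated or sized, and requiring all three would reduce power.

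**5. Keeping three primary visits with a split alpha.** 4%/3 = 1.33% each. With the convention that reproduces 411, this needs 180 + 360 = 540 evaluable patients; two-sided, 207 + 414 = 621. With 137 and 274 patients, power at 1.33% would be about 67% (one-sided) or 59% (two-sided). This applies the 6-week rates to all visits, which is an assumption.

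**The case against.** The strongest reply is that the analysis section describes one model and one test. Together with the sample size section, which says "For the first primary endpoint, proportion of patients with neurological deterioration at 6 weeks postsurgery", that gives one 6-week test at 4% and one residual-tumour test at 1%, and the 5% stands. The covariate rule also uses a single count of patients who deteriorate, which suits one binary outcome better than three. The three visits might only be an assessment schedule, and a visit hierarchy may exist in an analysis plan that is not shown.

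Much of this stands. A reader might infer from the outcomes section that three tests at 4% are planned and that the guarantee fails outright. The article does not support that: nowhere does it say that each visit is tested at 4%, or that one visit is enough. A reader might also multiply further for two separate mapping-versus-control comparisons. The article does not state those either: it tests one arm effect, and 411 reproduces only with the mapping arms pooled.

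What the reply does not remove is the conflict itself. To reach the safe reading, one must set aside the wording of both the abstract and the outcomes section. An unseen analysis plan could choose a visit, but the published endpoint definition would still disagree with the published sample size.

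**Conclusion.** The point holds as an inconsistency in the definition of a primary endpoint that leaves an explicit error guarantee unsecured. It is not a demonstration that the error is inflated. Overall error is 5% if there is one NIHSS test at 6 weeks. It would be about 7.8% (correlation 0.9) to 12.5% (correlation 0) if any of three 4% tests could succeed. That range rests on two assumptions the article does not make: the any-visit rule and the correlation values. Sidedness does not affect the two ends of the scale: independent visits give 1 − 0.96³ and perfectly correlated visits give 4%, whichever way the test is run.

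**What to change.** State in the abstract, in Primary outcome measures and in Primary study parameters that the confirmatory endpoint is NIHSS deterioration at 6 weeks, tested once at 4%. List 3 and 6 months as secondary, or test them in a stated fixed order, each at 4% and only if the preceding test is significant. Either version keeps endpoint 1 at 4% and the total at 5%. Settle this before outcomes by arm are examined.

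The cost is a wording change in three places. The evaluable sample stays at 411 and no visits or data are added. The small downside is that the later visits lose standalone primary status. If the sponsor wants all three to remain primary, the 4% has to be split or a single combining rule written down. An equal split would call for 540 to 621 evaluable patients on the assumptions above, or acceptance of lower power.

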#### Secondary outcome measures

The secondary outcomes are (1) PFS at 12 months defined as time from diagnosis to disease progression (occurrence of a new tumour lesions with a volume greater than 0.175 cm^3^, or an increase in residual tumour volume of more than 25%) or death, whichever comes first; (2) OS at 12 months defined as time from diagnosis to death from any cause; (3) oncofunctional outcome defined as the calculated coordinate of the extent of resection (or residual volume) on the x-axis and the postoperative NIHSS deterioration (delta NIHSS) on the y-axis and (4) frequency and severity of serious adverse events (SAEs) in each arm.

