### Inclusion criteria

In order to be eligible to participate in this study, a subject must meet all of the following criteria:

Age ≥18 years and ≤90 years.Tumour diagnosed as HGG (WHO grade III/IV) on MRI as assessed by the neurosurgeon.Tumours situated in or near eloquent areas; motor cortex, sensory cortex, subcortical pyramidal tract, speech areas or visual areas as indicated on MRI (Sawaya grading II and II).^19^The tumour is suitable for resection (according to neurosurgeon).Written informed consent.

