### Participant timeline

The flow diagram illustrates the main study procedures, including follow-up evaluations (figure 1). In summary, study patients are allocated to either the awake mapping, asleep mapping or no mapping group and will undergo evaluation at presentation (baseline) and during the follow-up period at 6 weeks, 3 months, 6 months and 12 months postoperatively. Motor function will be evaluated using the NIHSS and Medical Research Council (MRC) scales. Language function will be evaluated using a standard neurolinguistic test-battery consisting of the Aphasia Bedside Check (ABC), Shortened Token Test, Verbal fluency, Picture description and Object naming. Cognitive function will be assessed using the Montreal Cognitive Assessment (MoCA). Patient functioning with be assessed with the Karnofsky Performance Scale (KPS) and the ASA (American Society of Anesthesiologists) physical status classification system. Health-related quality of life (HRQoL) will be assessed with the EQ-5D questionnaire (EuroQol Five Dimensions health questionnaire) and the QLQ-C30 and QLQ-BN20 questionnaires. OS and PFS will be assessed at 12 months postoperatively. We expect to complete patient inclusion in 4 years. The estimated duration of the study (including follow-up) will be 5 years.

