### Data analysis

All analyses will be according the intention to treat principle, restricted to eligible patients. Patients initially registered but considered ineligible afterwards based on the histological analysis on tissue extracted during surgery, will be excluded from all analyses.

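### PFS and OS are timed from an undated, apparently preoperative diagnosis, while the 12-month assessment is counted from surgery; the interval between them is guaranteed event-free

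*Protocol article*

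**What the plan says.** The protocol article gives two different starting points for the same endpoints.

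- **Secondary outcome measures** start the clock at diagnosis: "PFS at 12 months defined as time from diagnosis to disease progression" (or death, if earlier), and "OS at 12 months defined as time from diagnosis to death from any cause".
- **The abstract** (Methods and analysis) lists OS and "progression-free survival at 12 months after surgery".
- **Participant timeline:** "OS and PFS will be assessed at 12 months postoperatively".
- **Study procedures** give the last visit as "Twelve months postoperatively: PFS, OS (end of study").

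No section gives diagnosis a date for these endpoints. The nearest use of the word is an inclusion criterion: "Tumour diagnosed as HGG (WHO grade III/IV) on MRI as assessed by the neurosurgeon". That assessment comes before the operation. Under Data analysis, patients found ineligible "based on the histological analysis on tissue extracted during surgery, will be excluded from all analyses".

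Study monitoring states that allocation is not randomised. Under Secondary study parameters, the Cox models for PFS and OS adjust for age group, KPS and hemisphere. They mention neither the interval from diagnosis to surgery nor delayed entry at surgery.

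**The concern.** A 12-month proportion has a meaning only relative to a start date, and the article supplies two. Two analysts working from different sections would report different 12-month PFS and OS from the same patients.

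The choice also matters for validity. A patient who dies between the MRI and the operation has no operation and no operative tissue on which eligibility could be confirmed. Everyone analysed has therefore survived that interval. Progression of residual tumour cannot be recorded in it either, because there is no residual until after resection. Starting the clock at an MRI diagnosis adds a stretch in which these events cannot happen: immortal time.

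If the stretch were equal in all arms, it would inflate each arm's 12-month figures and leave the contrast roughly intact. If one arm waits longer, that arm is credited with the extra time as survival. Without randomisation nothing in the design equalises the waits, and the stated Cox model does not correct for them.

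**Working it through.** The article states no power, event count or expected rate for PFS or OS, so there is no figure of its own to reproduce. The check has a reading step and an illustration.

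**1. Does the interval contain guaranteed time?** It depends on what diagnosis means.

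- Preoperative MRI, as in the inclusion criteria: surgery comes later, and survival to surgery is a condition of being analysed. The interval is guaranteed event-free for death and for residual growth.
- Histology on the operative tissue, the basis for exclusion under Data analysis: the start date is close to surgery and the guaranteed time largely vanishes.

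The text does not choose between them. Its only explicit use of the word for entry is the MRI one.

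**2. Effect on 12-month OS.** Assumptions, none from the article: survival after surgery is exponential with median m months, and the treatment effect is nil. With a wait of d months before surgery, survival 12 months after diagnosis is

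S(12 − d) = 2^(−(12 − d)/m),

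against S(12) = 2^(−12/m) with no wait. Two weeks is d = 0.46 and four weeks d = 0.92.

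| Median m | No wait | 2 weeks | 4 weeks |
|---|---|---|---|
| 12 | 50.0% | 51.3% (+1.3) | 52.7% (+2.7) |
| 15 | 57.4% | 58.7% (+1.2) | 59.9% (+2.5) |
| 18 | 63.0% | 64.1% (+1.1) | 65.3% (+2.3) |

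Gains are computed before rounding. At m = 15 and four weeks: 2^(−11.08/15) = 0.599 against 2^(−12/15) = 0.574.

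**3. Effect on an arm comparison.** Now let two arms have identical survival from surgery, one waiting 0.5 month and the other 1.5 months (assumed).

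- 12-month OS differs by 2.5 to 3.1 points for medians of 18 to 12 months.
- 12-month PFS differs by about 3.3 points for assumed medians of 6 to 9 months.
- An unadjusted Cox model timed from diagnosis gives a hazard ratio of about 0.89 for OS (median 15) and 0.86 for PFS (median 7), where the true value is 1.
- With equal waits of 0.5 month, the difference is zero and the hazard ratio is 1.

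**4. After the fix.** Timed from surgery, d drops out of the formula. With identical survival from surgery the arm difference is zero whatever the waits.

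**The case against.** The case for leaving this alone has four parts.

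*Diagnosis may mean histology.* The MRI wording is an entry criterion, not a time origin, and eligibility is finally settled on tissue. This stands as a possibility: under that reading little remains beyond the inconsistent wording. It does not answer the point, because the article never dates diagnosis.

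*The guaranteed time is common to all arms.* Correct. The arm contrast is biased only if waits differ, and the article gives no waiting times.

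*The effect is small.* With 137 per arm and 57.4% alive at 12 months, the standard error of an arm difference is √(2 × 0.574 × 0.426/137) = 0.060, a 95% half-width of about 12 points. A shift of 2.5 points is under half a standard error, on an unpowered secondary endpoint in a study that already declares possible bias. This limits the severity. However, the shift is systematic, so a larger sample would not remove it.

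*Either clock can be analysed.* Also correct: follow-up to 12 months after surgery covers 12 months from an earlier diagnosis. So no data are lost, but the definition still has to say which clock is reported.

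A reader might go further and infer that the clock favours awake mapping because it needs an additional team in theatre. The article does not support that. Asleep mapping, with evoked-potential monitoring, is also demanding, and no scheduling data are given for any arm.

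**Conclusion.** The contradiction over the start date is certain from the text. That the interval from diagnosis to surgery counts as guaranteed event-free time follows if diagnosis means the preoperative MRI, which is how the article uses the word at entry. On that reading 12-month PFS and OS are inflated in all arms, and the arm comparison can be biased if waits differ. For 12-month OS the size is about 2.5 points per four extra weeks, assuming exponential survival with a 15-month median. Neither the median nor the waits come from the article, and no direction between arms can be claimed. The definition should be corrected, but this does not threaten the primary endpoints.

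A further inference lies close by in the same definition and should not be drawn. Progression of existing disease needs "an increase in residual tumour volume of more than 25" per cent with no absolute minimum, while a new lesion must exceed 0.175 cm³. The relative rule is the more sensitive below 0.7 cm³ (0.175/0.25), so one might conclude that it penalises the arms with better resection. The article does not support that direction: its sample-size section assumes contrast-enhancing residual in 75% of controls against 50% of mapping patients, so more controls are exposed to the rule. Adding a 0.175 cm³ floor is not a clear improvement either. Under proportional growth, a 0.1 cm³ remnant would have to reach 0.275 cm³, taking ln(2.75)/ln(1.25) ≈ 4.5 times as long to count as progressed.

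**What to change.** Under Secondary outcome measures, define PFS and OS from the date of surgery, so that the definition matches the abstract, the participant timeline and the follow-up schedule. Kaplan-Meier estimates and Cox models then use that origin.

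If the sponsor prefers to keep diagnosis as the origin, the article should say which event and date is meant (MRI or histology). The survival analyses should then admit patients to the risk set only from the date of surgery (delayed entry).

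The first option is an edit to the two definitions. Every follow-up visit is already counted from surgery, so the date has to be known, although the article's list of recorded items does not name it. The price is slightly less comparability with published series timed from diagnosis. Sample size, visits and the primary analyses are unaffected.
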